## Introduction

Gastroesophageal varices (GOV) bleeding is a common and serious complication of advanced liver cirrhosis with a median survival of less than 2 years. Despite the continuous improvement of treatments, the mortality rate within 6 weeks after GOV bleeding is as high as 15–25% [1]. Multiple guidelines have pointed out that transjugular intrahepatic portosystemic shunt (TIPS) is the rescue treatment of acute variceal hemorrhage (AVB) after failure of standard therapy and an effective second-line treatment for preventing patients with high risks from rebleeding of GOV [1–4].

The safety and stability of TIPS have been greatly improved due to the improvements of related technologies and the emergence of various novel devices, but the incidence of hepatic encephalopathy (HE) after shunting (10–50%) hindered the widespread use of TIPS [5]. Post-TIPS HE is defined as a brain dysfunction caused by TIPS, it manifests as a wide spectrum of neurological or psychiatric abnormalities ranging from subclinical alterations to coma [6, 7]. None of the administration of aspartic acid/ornithine [8], lactulose [9], or albumin [10] has been proven to effectively prevent the occurrence of HE after TIPS.

On the other hand, the target portal vein branch might affect the incidence of HE after TIPS. The anatomical study suggested that the blood of the portal vein is composed of superior mesenteric venous blood rich in intestinal toxin and splenic venous blood which is relatively. The laminar flow effect may cause the majority of splenic venous blood flow to enter the left branch of the portal vein while the majority of superior mesenteric vein blood flow enters the right branch of the portal vein. An experimental study also found that the blood ammonia concentration in the right branch of the rabbit portal vein was significantly higher than that in the left branch. Some researchers observed that compared with shunting the right branch of the portal vein, the incidence of HE after shunting the left branch was significantly reduced (15.4~28.7% vs 37.5~56.0%) [11–13]. However, the current TIPS-specific stent is applied in none of the above clinical studies, the diameter of the implanted stent is not uniform, the indications for the patients receiving TIPS treatment are different, and the definition of HE after shunting is inconsistent.

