### Outcome measures

The primary endpoint of the INTIPHE trial is to compare the rate of post-TIPS overt hepatic encephalopathy between patients with left or right shunt at 24 months.

The secondary endpoints include comparing the grade and duration of hepatic encephalopathy, covert HE, the rate of shunt dysfunction, the rate of variceal rebleeding, the HE free survival, the cumulative patency rate of stent and the overall survival at 24 months between two groups.

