### Outcome definitions

The grade of HE was classified into covert HE (minimal HE and grade I) and overt HE (grade II to grade IV) according to the severity of manifestation (Table 3). Stroop Test (EncephalApp developed by Jasmohan Bajaj) will be used to detect the minimal HE. An off-time and on-time value >190 s will identify a patient with covert HE. Grade I to grade IV HE will be diagnosed by clinical examination. The starting time, duration, treatment, and outcome of every episode will be recorded.

**Table 3 Tab3:** WHC and clinical description of HE

WHC	ISHEN	Description
Minimal	Covert	Psychometric or neuropsychological alterations of tests exploring psychomotor speed/executive functions or neurophysiological alterations without clinical evidence of mental change
Grade I		Trivial lack of awareness Euphoria or anxiety Shortened attention span Impairment of addition or subtraction Altered sleep rhythm
Grade II	Overt	Lethargy or apathy Disorientation for time Obvious personality change Inappropriate behavior Dyspraxia Asterixis
Grade III		Somnolence to semi stupor Responsive to stimuli Confused Gross disorientation Bizarre behavior
Grade IV		Coma

HE-free survival (HEFS) is defined as the time from D0 to the first episode of HE.

Shunt dysfunction will be suspected in the condition of rebleeding and/or the maximum flow velocity within the shunt is less than 0.5 m/s or absent on color Doppler ultrasound (CDUS). Shunt will be further confirmed by portography if the shunt stenosis is greater than 50% and/or portal-systemic gradient (PSG) is beyond 15 mmHg, and TIPS revision by balloon angioplasty and additional stent-placement will be planned.

Variceal rebleeding is defined as bleeding from gastroesophageal varices confirmed by upper gastrointestinal endoscopy.

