### Sample size calculation

There is currently no multi-center RCT study on comparing the rate of HE between HBV-related cirrhosis patients with shunting left/right portal vein branches. The sample size was determined on the basis of three single-center study [11–13]: the rate of HE in the patients with left branch shunt was 19.4% (2 years after TIPS), 15.4% (2 years after TIPS) and 22.6% (1 year after TIPS), while the rate of HE in the patients with right branch shunt was and 43.8% (2 years after surgery), 37.5% (2 years after surgery), and 28.6% (1 year after surgery). We presume that the rate of HE after 2 years of TIPS shunting left and right branches will be 16.9% and 33.1%, respectively. Considering a power of 80% with a bilateral alpha risk of 5% and a dropout rate of 10%, we aimed to enroll 130 patients.

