### Statistical analysis

All data will be analyzed on the intention-to-treat population and are supplemented by per-protocol set analyses. The intention-to-treat population contains all patients who will undergo randomization (irrespective of whether they successfully receive TIPS), while per-protocol set analyses only include patients who successfully receive TIPS. Continuous variables will be summarized as mean ± standard deviation or the median values (ranges) and will be compared using the independent sample *t* test or one-way analysis of variance. Categorical variables will be expressed as frequencies and compared using the Chi-Square or Fisher’s exact tests. The missing data were performed with multiple imputation by using the MICE procedure. The time-to-event primary and secondary outcomes will be calculated by the Kaplan-Meier method and compared by the log-rank test (Mantel-Haenszel version). Data will be censored when any of the following events occur : liver transplantation, death, end of follow-up time. Estimates of treatment effect (with 95% CIs) were evaluated by using Cox regression models. Two-tailed *p* values <0.05 will be considered statistically significant. All statistical calculations will be performed using SPSS V.25.0 (Chicago, IL, USA).

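### A single censoring rule that lists death covers every time-to-event outcome, which contradicts overall survival and turns HE-free survival into time to first HE

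*Protocol article*

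**What the plan says.** Under Statistical analysis, the protocol article first sets the scope: "The time-to-event primary and secondary outcomes will be calculated by the Kaplan-Meier method and compared by the log-rank test". It then gives one censoring rule: "Data will be censored when any of the following events occur : liver transplantation, death, end of follow-up time". Treatment effects are to be estimated by Cox regression. No outcome is exempted from the rule.

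The outcomes in scope are listed under Outcome measures. The primary endpoint is to "compare the rate of post-TIPS overt hepatic encephalopathy between patients with left or right shunt at 24 months". The secondary endpoints include "the HE free survival, the cumulative patency rate of stent and the overall survival at 24 months between two groups". The Abstract, the end of the Introduction and the Discussion also name overall survival as an outcome.

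Under Outcome definitions, "HE-free survival (HEFS) is defined as the time from D0 to the first episode of HE". Death is not part of that definition. The same section divides HE into covert (minimal and grade I) and overt (grades II to IV), and the definition does not say which of these counts.

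Nowhere does the article name death as the event for overall survival, add it to HE-free survival, or treat it as a competing event.

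**The concern.** One rule cannot serve both an outcome whose event is death and outcomes for which death only ends observation. For overall survival, censoring at death removes every event, so a declared secondary endpoint cannot be computed from the only rule written.

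For HE-free survival, the definition and the rule agree with each other, but what they describe is time to first HE. A reader who sees a 24-month HE-free survival percentage will take it as the proportion alive without HE. With deaths censored it is not that. Its complement is also not the proportion who develop HE, because it estimates what would be seen if nobody died. The second problem reaches the primary endpoint as well if the 24-month HE rate is read from a Kaplan-Meier curve, as the reference to a time-to-event primary outcome suggests.

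Deaths should be expected. The Introduction describes variceal bleeding in advanced cirrhosis as a complication "with a median survival of less than 2 years". That is a background figure and not a forecast for this trial, which enrols Child-Pugh A or B only.

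**Working it through.** **Overall survival.** No arithmetic is needed. The endpoint is in scope, the event it needs is death, and the rule makes every death a censoring. The result is 0 events, a Kaplan-Meier curve that stays at 100%, and a log-rank test and Cox hazard ratio that cannot be computed.

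**HE-free survival and HE incidence.** The article has no planning figure for mortality or HE-free survival to reproduce. Its one sample-size figure does not bear on this point. What follows is an illustration.

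Inputs:
- 24-month HE rates from Sample size calculation: "left and right branches will be 16.9% and 33.1%, respectively". They are taken here as death-censored rates (an assumption).
- Net 24-month death probability d, meaning the probability of death if HE is left out of account: 20%, range 10–30% (an assumption; the document gives none).
- Deaths equally likely in both arms, independent of HE, constant hazards (assumptions).
- 65 patients per arm (130 at 1:1), without dropout.

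Cumulative hazards over 24 months:
- HE, left: −ln(0.831) = 0.185. HE, right: −ln(0.669) = 0.402.
- Death at d = 20%: −ln(0.8) = 0.223.

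*Kaplan-Meier with death censored* = 1 − HE rate: 83.1% (left), 66.9% (right), whatever d is.

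*Alive and HE-free* = (1 − HE rate) × (1 − d):
- Left: 0.831 × 0.8 = 66.5%; from 0.831 × 0.7 = 58% to 0.831 × 0.9 = 75%.
- Right: 0.669 × 0.8 = 53.5%; from 0.669 × 0.7 = 47% to 0.669 × 0.9 = 60%.

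*Cumulative incidence of HE* = HE hazard ÷ (HE hazard + death hazard) × (1 − proportion alive and HE-free):
- Left: 0.185/0.408 × 0.335 = 15.2%.
- Right: 0.402/0.625 × 0.465 = 29.9%.

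By the same split, d = 20% means about 18.3% (left) and 16.6% (right) die before any HE.

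*Hazard ratio, left versus right*:
- HE alone: 0.185/0.402 = 0.46.
- HE or death: (0.185 + 0.223)/(0.402 + 0.223) = 0.65.

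| | d = 10% | d = 20% | d = 30% |
|---|---|---|---|
| HE incidence from 1 − KM, left / right | 16.9% / 33.1% | 16.9% / 33.1% | 16.9% / 33.1% |
| Cumulative incidence of HE, left / right | 16.1% / 31.5% | 15.2% / 29.9% | 14.3% / 28.2% |
| Hazard ratio, HE alone | 0.46 | 0.46 | 0.46 |
| Hazard ratio, HE or death | 0.57 | 0.65 | 0.71 |
| HE-free survival events, death censored | 31 | 29 | 28 |
| HE-free survival events, death counted | 42 | 52 | 62 |
| Overall survival events, rule as written | 0 | 0 | 0 |
| Overall survival events, death as event (130 × d) | 13 | 26 | 39 |

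**The case against.** The best defence is that the overall survival conflict is a drafting slip. The term itself implies death as the event, survival is recorded at every visit in Table 2, and the censoring sentence fits the HE, patency and rebleeding analyses. No analyst is likely to code overall survival with no events. That is fair as to intent, and a reader should not infer that the survival data will be lost. It does not remove the contradiction. Detail missing from an article can be left to a statistical analysis plan, but this is a rule that the article states, with a scope that includes overall survival.

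For HE-free survival, the defence is that definition and rule are explicit and consistent. Together they give a coherent time-to-first-HE analysis, and death-censored log-rank and Cox results are valid for the cause-specific HE hazard. This stands. What remains is a misleading name and a Kaplan-Meier percentage that answers a different question from the one its name suggests.

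Two stronger readings are tempting, and the documents support neither:
- A reader might infer that a patient who dies without HE is carried forward as HE-free. Under Kaplan-Meier a censored patient leaves the risk set.
- A reader might infer that HE-free survival would look better in the arm with more early deaths, masking a survival harm. Under independent hazards the curve does not move with mortality: it is 83.1% and 66.9% at every value of d above. That bias would need informative censoring, with those who die also being at higher risk of HE. This may be plausible in cirrhosis, but nothing in the document shows it. Overall survival is also a separate endpoint.

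The size of the illustration rests on an assumed death rate. The background survival figure cannot be carried over to a Child-Pugh A or B population, so the results are given as a range.

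**Conclusion.** The point holds in two parts of different kinds. The first is a direct contradiction between Statistical analysis and Outcome measures: under the written rule overall survival has 0 events. It needs no assumption, and the intended reading is obvious.

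The second is that HE-free survival, as defined and censored, is time to first HE. The between-arm tests keep a valid cause-specific meaning, but the percentages do not mean what the label says. At an assumed 20% net death probability, reported HE-free survival exceeds the proportion alive and HE-free by 83.1 − 66.5 = 16.6 points (left) and 66.9 − 53.5 = 13.4 points (right). HE incidence is overstated by 16.9 − 15.2 = 1.7 and 33.1 − 29.9 = 3.2 points. Counting death as an event moves the hazard ratio from 0.46 to about 0.65 (0.57–0.71 over the range), so the two readings of the endpoint differ materially. These sizes depend on the assumed mortality, equal in both arms, on independent constant hazards, and on treating the planning rates as death-censored.

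Correcting the rule for overall survival alone would leave the second part in place, because the HE-free survival definition also omits death.

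**What to change.** Replace the single rule under Statistical analysis with a short list of event and censoring rules by outcome:

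- **Overall survival:** the event is death from any cause. Death is removed from the censoring list for this outcome.
- **HE-free survival:** the event is first HE or death from any cause, whichever comes first, with the grade of HE that counts stated, because the present definition says HE without restricting it to overt HE. Alternatively, keep the present definition and rename the outcome time to first HE. In either case, amend Outcome definitions to match.
- **HE, rebleeding and stent patency:** report incidence as cumulative incidence with death as a competing event. Death-censored log-rank and Cox analyses can stay, described as comparisons of cause-specific hazards.

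The cost is wording in the protocol or analysis plan plus one added estimate per outcome. No new data are needed, since survival and HE are already assessed at every visit in Table 2. The change should be made before outcomes are examined by treatment group, because choosing between the two HE-free survival definitions afterwards would be data-dependent.

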## Methods

### Study design

This study is a randomized, controlled, single-blind, multicenter superiority trial with two parallel groups, comparing the influence of shunting the left or right branch of the portal vein on post-TIPS hepatic encephalopathy in patients with HBV-related cirrhosis. A total of 130 patients will be recruited over a period of 24 months across 5 centers in China. Centers will be chosen based on their potential to recruit a high number of patients and their expertise in TIPS treatment and will receive special training with standard TIPS procedures and HE assessment. Eligible patients will be stratified 1:1 to constructing either a left or right portal vein shunt with an 8-mm Viatorr stent (Fig. 1).

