### Randomization

Eligible patients will be randomized 1:1 into shunting the left (L Group) or right (R Group) branch of the portal vein. The randomization will be stratified by center, Child-Pugh class (Child-Pugh Class A=5–6 points or Child-Pugh Class B=7–9 points), and the serial ammonia level (lower level ≤ 50 µmol/L or higher level >50 µmol/L) before TIPS. The list will be balanced by different-sized blocks and randomly alternated. The treatment assignment of each eligible patients was generated by the web-based system and was contained in opaque envelopes. This randomization procedure was performed by the coordinator, who was isolated from data collection and analysis. The data coordination center of Zhongshan Hospital will prepare the randomization. Patients and clinicians will not be blinded to the shunting branch of the portal vein in TIPS, so the investigators who perform data evaluation and analysis will not participate in the randomization and treatment.

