### Study limitations

Some aspects of the INTIPHE study design are worth further discussion. First, patients with HBV-related cirrhosis, which is the most common cause of liver cirrhosis in China instead of alcohol abuse in Western countries, are our target population. The difference in the etiology of liver cirrhosis might influence the application of our findings in Western countries. Second, eligible patients in the INTIPHE study will be stratified according to the Child-Pugh score as this is an independent prognostic factor of post-TIPS HE. In addition, patients will be stratified by serial ammonia concentration since it is associated with post-TIPS HE despite not being a valid tool to diagnose HE. Third, the rate of post-TIPS HE has been chosen as the primary endpoint as the episode of HE is a better quantitative indicator than the severity or duration of HE. Fourth, an 8-mm Viatorr covered stent was employed in the INTIPHE trial as recent studies found that compared to the 10mm covered stent, implantation of an 8-mm covered stent significantly reduced the incidence of HE after TIPS without affecting the shunt efficiency. Fifth, while blinding to the physicians is not possible due to the treatment methods, the potential biases caused by the lack of physician blinding will be minimized by appointing an independent group of physicians performing the blind follow-up and diagnosis of post-TIPS HE.

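### The log-rank test is named without the randomisation strata and the Cox terms are not stated: valid, but conservative if the strata are prognostic

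*Protocol article*

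**What the plan says.** Under Randomization, the protocol article states: "The randomization will be stratified by center, Child-Pugh class", and adds "the serial ammonia level (lower level ≤ 50 µmol/L or higher level >50 µmol/L) before TIPS". Study design gives five centres and 130 patients.

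Study limitations gives the reason for two of the three factors: "eligible patients in the INTIPHE study will be stratified according to the Child-Pugh score as this is an independent prognostic factor of post-TIPS HE". It then says that ammonia is used because it is associated with HE after TIPS.

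Under Statistical analysis, the time-to-event primary and secondary outcomes are to be "calculated by the Kaplan-Meier method and compared by the log-rank test (Mantel-Haenszel version"). On the effect estimate it says: "Estimates of treatment effect (with 95% CIs) were evaluated by using Cox regression models". The section also fixes the censoring events, the two-sided 5% level and the software. None of the three stratification factors appears there.

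**The concern.** Stratified randomisation balances the arms on the chosen factors. If those factors predict the outcome, the treatment comparison varies less from trial to trial than it would under simple randomisation. An unstratified log-rank test does not credit that reduction. It uses a variance that is too large, so it rejects less often than its nominal level under the null and gives up some power under the alternative.

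At stake is efficiency, together with agreement between design and analysis. There is also a smaller point of pre-specification. While the Cox terms are unstated, an adjusted and an unadjusted hazard ratio could both be produced and either one presented as the main result.

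**Working it through.** **The plan's own figure.** Sample size calculation gives 16.9% (left) and 33.1% (right) at two years, 80% power, two-sided 5%, 10% dropout, N = 130. This does not reproduce.

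- Two proportions, pooled variance, mean risk 0.25: n per arm = [1.96·√(2·0.25·0.75) + 0.8416·√(0.169·0.831 + 0.331·0.669)]² / 0.162² = 111, so 222 in total and 222/0.9 = 247 with dropout.
- Log-rank (Schoenfeld): HR = ln(0.831)/ln(0.669) = 0.461; events = 4·(1.96 + 0.8416)²/(ln 0.461)² = 53; 53/0.25 = 212, and 212/0.9 = 236.
- Across the two-sided variants tried, the total with dropout is 236 to 276.
- Power at the stated rates is 57% (proportions) or 60% (Schoenfeld) with 130 patients, and 53% or 55% with 117 evaluable (130 × 0.9).

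This shortfall is a separate matter. It is given here because it sets the baseline power for what follows.

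**Size of the strata.** 5 centres × 2 Child-Pugh classes × 2 ammonia levels = 20 cells, and 130/20 = 6.5 patients per cell. Expected events are 130 × 0.25 = 32.5, or about 1.6 per cell. Child-Pugh by ammonia alone gives 4 strata, averaging 32.5 patients and about 8 events each.

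**The tests compared.** The unstratified statistic is z = (O − E)/√V over all patients. The stratified one is z = Σ(Oₛ − Eₛ)/√ΣVₛ, summed over strata s.

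**Simulation.** 15,000 trials per setting, blocked randomisation within the 20 cells, exponential times followed to two years, marginal risks held at 33.1% and 16.9%. Not in the document and therefore assumed: 60% Child-Pugh B, 50% high ammonia, centres of equal expected size, blocks of 2 and 4, the prognostic HR for each factor, and a between-centre SD of the log hazard. Monte Carlo standard error is about 0.2 points for type I error and 0.4 for power. All tests were applied to the same simulated trials. Results for N = 130, in percent:

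| Prognostic HR per factor (centre SD) | Type I: unstratified | Type I: 4 strata | Type I: 20 cells | Power: unstratified | Power: 4 strata | Power: 20 cells | Power: Cox adjusted for the two factors |
|---|---|---|---|---|---|---|---|
| 1.0 (0) | 4.9 | 4.8 | 4.9 | 57.6 | 57.3 | 55.7 | 56.5 |
| 1.5 (0.2) | 4.7 | 5.0 | 5.0 | 58.1 | 58.6 | 57.2 | 57.6 |
| 2.0 (0.3) | 4.0 | 4.8 | 4.9 | 58.0 | 59.6 | 58.7 | 58.7 |
| 3.0 (0.5) | 3.1 | 4.3 | 4.8 | 59.2 | 64.1 | 64.5 | 63.3 |

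- Change in power from unstratified to 4 strata: −0.3, +0.5, +1.6 and +4.9 points.
- With N = 117, the unstratified test has 53.0 to 54.3% power. The 4-stratum test has 53.5, 53.5, 56.0 and 59.3% down the same rows, a gain of 5.2 points at HR 3.
- In the last row the 4-stratum test is still slightly conservative (4.3%), because that setting also gives centre an effect, which four strata leave out.

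**A second simulation.** 4,000 trials per setting, 10% dropout, blocks of 2, 4 and 6; Monte Carlo standard error about 0.8 points for power. Power for unstratified / 4 strata / 20 cells:

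- HRs 2.0 and 1.8: 56.0 / 57.6 / 55.0%.
- HRs 3 and 2: 56.6 / 60.2 / 58.0%.
- HRs 3 and 3: 57.2 / 63.6 / 59.6%.

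Type I error, unstratified against stratified, was 4.1 against 5.4% at HRs 3 and 2, and 3.3 against 5.0% at HRs 3 and 3. The direction and rough size agree with the table. At HR 3 for both factors the 4-stratum gain is 6.4 points.

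**What the type I error implies.** A rejection rate of 3.1% at |z| > 1.96 corresponds to a normal cut-off of 2.157, so the true variance of the statistic is about (1.96/2.157)² = 83% of what the unstratified test assumes. At 4.0% it is (1.96/2.054)² = 91%, and at 4.7% it is (1.96/1.986)² = 97%.

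**The case against.** The strongest reply is that this is detail for the statistical analysis plan. The source is a condensed article, and covariates and strata are commonly fixed elsewhere. For the Cox model this stands. A reader might infer that the model ignores the stratification factors, but the article lists no terms at all, so it cannot be said to contain treatment only. For the test the reply is weaker. The section names the test and its version, the censoring events, the level and the software, and a log-rank test described that fully without strata is unstratified as written. The wording "compared by the log-rank test (Mantel-Haenszel version") names a form of the test; it does not announce stratification by baseline factors.

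Second, the prognostic strengths are assumed. This also stands. A reader might take a loss of power as established, but the document gives no strengths, and with weak factors there is nothing to gain. A gain near 5 points needs an HR of about 3 for both factors, a ninefold hazard range between extreme strata (3 × 3). The eligibility criteria (Child-Pugh A or B only, limits on bilirubin and ammonia, no previous overt HE) may well narrow that range.

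Third, matching the randomisation fully would mean 20 cells, which costs about 1 to 3 points when the factors are weak. That is correct, and it is why the remedy leaves centre out of the primary analysis.

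Fourth, an unadjusted hazard ratio is not wrong; it targets a different quantity. In the simulation, the same marginal risks correspond to an HR of 0.461 with no prognostic effect and about 0.42 within strata at a prognostic HR of 3. No bias is alleged here.

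**Conclusion.** The point holds as one of efficiency and consistency. The randomisation uses three factors, the protocol presents two of them as related to the outcome, and the log-rank test as written uses none. If those two matter, the test is conservative: type I error at N = 130 is about 4.7%, 4.0% and 3.1% for assumed prognostic HRs per factor of 1.5, 2 and 3. The power forgone is about 0 to 2 points up to an HR of 2 and about 5 to 6 points at 3. If they do not matter, stratifying on them costs about 0.3 points.

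Two stronger conclusions are not supported. The test is not invalid, since type I error is never inflated in these settings. Nor would stratifying restore the planned power: even the most favourable setting leaves it near 64%, against the stated 80%.

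These sizes rest on the assumed prognostic HRs, stratum shares, centre effects and exponential times. Deaths and transplants as censoring events were not modelled.

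**What to change.** Before unblinding, and ideally before the interim analysis on the same endpoint, state the following:

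- The primary test is a log-rank stratified by Child-Pugh class (A/B) and ammonia (≤50 / >50 µmol/L), using the values recorded at randomisation.
- The primary hazard ratio, with its 95% CI, comes from a Cox model stratified by or adjusted for the same two factors. Choose one, and say that the estimate is conditional on them.
- Centre is handled in a sensitivity analysis, because 20 cells are too sparse for about 30 events.
- The unstratified log-rank is reported as supportive.

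The cost is a few lines of text. No new data are needed, since both factors are known for every patient at randomisation. The shortfall in sample size has to be dealt with separately.
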